### Secondary outcomes

Secondary outcomes include the association of complicated AHA-LT VI plaques with specific infarct patterns (territorial infarcts, multiple embolic infarcts, small lacunar lesions), with aortic arch plaques as determined by transoesophageal echocardiography or computed tomography angiography (CTA) and their association with biomarkers derived from serum and plasma. Furthermore, we will evaluate the recurrence rate of ischemic events and the rate of new ischemic lesions on brain MRI in patients with complicated AHA-LT VI plaques after twelve months follow up. In addition, we will investigate whether specific features of complicated AHA-LT VI plaques, such as intraplaque hemorrhage and thin or ruptured fibrous cap are associated with an increased progression rate of atherosclerotic disease burden after twelve months.

Recurrent ischemic events include cerebrovascular and cardiovascular events. Cerebrovascular events are defined either clinically (TIA, amaurosis fugax or stroke), by brain MRI alone (new ischemic lesion on brain MRI) or on the combined assessment of clinical findings and brain MRI. Furthermore, the most likely cause of the recurrent cerebrovascular event is classified according to the ASCO and TOAST classifications. Unilateral events in the anterior circulation will be included in the final analysis to estimate the risk of recurrent events in patients with AHA-LT VI plaques. Recurrent ischemic events in other territories, bilateral events and cardiovascular events (myocardial infarction, vascular death) are recorded during follow-up to evaluate if patients with complicated AHA-LT VI plaques have a higher overall atherosclerotic disease burden.

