### Sample size

Based on a pilot study by Freilinger et al. [24], we estimated that 40% of ipsilateral carotid artery plaques in patients with a cryptogenic stroke are complicated AHA-LT VI plaques. Thus, in 100 patients with cryptogenic stroke the prevalence can be assessed with a precision of +/− 10%. Our unpublished pilot data indicate a prevalence of complicated AHA-LT VI plaques in patients with defined stroke etiology of about 10%. To determine this difference with a power of 80% and 5% level of significance, 32 patients of each group (cryptogenic and control group) would be sufficient. Assuming a prevalence of complicated AHA-LT VI plaques of 30% in the cryptogenic stroke group, 64 patients in each group are needed.

The recurrence rate of ischemic stroke associated with complicated AHA-LT VI plaques will be determined as the time period until the next ischemic event. Assuming a recurrence rate of ischemic events of 8% [35] within 12 months following the index stroke and a hazard ratio of AHA-LT VI plaques ≥ 5 [19,34,35], 300 patients will be enough to demonstrate a significant difference in event rates between patients with and without AHA-LT VI plaques.

Previous longitudinal studies, which demonstrated associations of intraplaque hemorrhage with accelerated plaque progression and with new surface disruption, were able to show those associations with much smaller sample sizes [21,36]. Thus 300 patients will provide sufficient power to detect effects of certain plaque features on plaque progression.

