**Figure 1 F1:**
[figure not shown]
**Axial images of specific AHA-LT VI plaque features in a patient with acute ischemic infarct.** High-resolution black blood MRI of the carotid arteries demonstrate a large eccentric plaque with <50% stenosis in the right carotid artery, hyperintense on T1w, T2w and PDw sequences consistent with fresh intraplaque hemorrhage (**A**, arrow). Axial images 0.6 cm above the bifurcation show an area attached to the plaque, which is hypo- to isointense on T1w + CM, PDw and TOF, consistent with a mural thrombus (**B**, arrow). (T1w: T1-weighted black blood sequence, PDw: PD-weighted sequences, T2w: T2-weighted sequence, TOF: Time-of-flight MR angiography, T1w + CM: T1-weighted black blood sequence after contrast administration).

All carotid and brain MRI examinations will be evaluated by two radiologists blinded to the clinical status. In case of discordant results, a consensus decision will be made. Image quality is rated on a five point scale (1 = worst, 5 = best), with MRIs ≥3 included for further analysis [31].

New ischemic lesions on brain MRI during follow up are defined as hyperintense lesions clearly visible on T2 weighted sequences.

All statistical analyses will be performed using SPSS and SAS. For determination of differences in prevalence of complicated AHA-LT VI plaques between patients with cryptogenic stroke and stroke with defined etiology the Chi square test will be used. Differences in the prevalence of complicated AHA-LT VI plaques ipsi- and contralateral to the ischemic stroke will be calculated using the McNemar Test. For the cross-sectional analysis the prevalence of AHA-LT VI plaques in patients with territorial infarcts, multiple embolic infarcts and small lacunar lesions will be compared. Furthermore, the difference in prevalence of AHA-LT VI plaques in patients with aortic arch plaques < 3 mm and > 3 mm will be determined. Data from the serial plaque study are analyzed in accordance to previous studies [38]. The effect of plaque morphology on cerebrovascular (TIA, amaurosis fugax and stroke) and cardiovascular events (myocardial infarction, vascular death) will be assessed using Cox proportional-hazards regression analysis. Cohen’s kappa test will be employed to evaluate the intra- and inter-reader agreement for identification of AHA-LT VI.

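### The recurrence analysis counts unilateral anterior events on either side of the brain, without tying them to the artery that carries the AHA-LT VI plaque, so the hazard ratio is likely to be diluted; three sections also name different recurrence endpoints

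*Protocol article*

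**What the plan says.** The protocol article describes recurrence in three places.

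- **Secondary outcomes** fixes which events enter the plaque-risk analysis: "Unilateral events in the anterior circulation will be included in the final analysis to estimate the risk of recurrent events". Other events are kept apart to describe general disease burden: "Recurrent ischemic events in other territories, bilateral events and cardiovascular events (myocardial infarction, vascular death) are recorded during follow-up". A unilateral anterior event in the hemisphere opposite the plaque is not named among those set aside.
- **Sample size** says that recurrence "will be determined as the time period until the next ischemic event". It assumes 8% ischemic events within 12 months and "a hazard ratio of AHA-LT VI plaques ≥ 5", and concludes that "300 patients will be enough to demonstrate a significant difference in event rates between patients with and without AHA-LT VI plaques". Exposure is a property of the patient, and no side is given for the 8% or for the hazard ratio.
- **Imaging and statistical analysis** plans Cox regression for "The effect of plaque morphology on cerebrovascular (TIA, amaurosis fugax and stroke) and cardiovascular events", again without a side.

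Recurrent cerebrovascular events are also classified by cause (ASCO and TOAST), but this classification is not used to select events.

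**The concern.** The study is built on laterality. Entry requires DWI lesions in the territory of a single internal carotid, the primary outcome is the ipsilateral plaque with the opposite artery as comparator, and the Discussion names arterio-arterial embolism as the mechanism. A carotid plaque can send emboli only into its own territory. The event rule already moves bilateral and other-territory events to the disease-burden question. An infarct in the opposite hemisphere belongs there by the same reasoning, yet as written it counts toward plaque risk.

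Such events occur in patients with and without the plaque, so they pull the hazard ratio toward 1. That estimate is meant to help plan interventional studies. Separately, the 8% and the hazard ratio of at least 5 are not tied to the endpoint that the Secondary outcomes section fixes.

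**Working it through.** **Inputs from the protocol article.** N = 300; 8% events at 12 months; HR 5; AHA-LT VI prevalence 40% in cryptogenic stroke and about 10% in defined etiology (Sample size); 40% of patients cryptogenic, and 37% ipsilateral versus 3% contralateral plaques in the interim cryptogenic data (Discussion); 36 months of clinical follow-up (Discussion); significance level 5%, taken as two-sided.

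**Derived.** Exposed share of patients: 0.40 × 0.40 + 0.60 × 0.10 = 0.22. Events at 12 months: 300 × 0.08 = 24.

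**1. The plan's own figure.** Schoenfeld: events = (1.96 + 0.84)² / [p(1 − p)(ln HR)²]. With p = 0.22 and HR 5, 7.85 / (0.1716 × 2.590) = 17.7, so 18 events for 80% power, or 225 patients at 8%. With 24 events power is 90%. So 300 patients suffice at a patient-level HR of 5. The exposed share matters: 24 events give 66% power at a 10% share and 97% at 40%.

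**2. Dilution (assumed).** Let HR 5 act only on the plaque side, and let a share s of background unilateral anterior events arise on the other side. The either-side HR is 5(1 − s) + s. Neither premise is in the documents, so a range is shown, with 24 either-side events and p = 0.22:

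| s | Either-side HR | Events for 80% power | Power, Schoenfeld | Power, simulated log-rank |
|---|---|---|---|---|
| 0 | 5.0 | 18 | 90% | – |
| 0.25 | 4.0 | 24 | 80% | about 88% |
| 0.5 | 3.0 | 38 | 61% | about 78% |

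The two methods differ because Schoenfeld is conservative here, with few events, a small exposed group and a large HR. They should not be mixed within one comparison.

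**3. Artery as the unit.** At s = 0.5 with 8% events, simulation gives about 95% power, against 78% under the plan's rule. With 4% events (assumed), it is 74% against 51%. Schoenfeld shows the same direction. The exposed share of arteries is (22% + 3%)/2 = 12.5%, applying the interim 3% contralateral figure to the whole cohort. Power is then Φ(ln 5 × √(24 × 0.125 × 0.875) − 1.96) = Φ(2.61 − 1.96) = 74%, against 61%.

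**4. Follow-up of 36 months.** At an assumed constant 8% per year, events are 300 × (1 − 0.92³) = 66.4. At HR 3, Schoenfeld power is Φ(1.099 × √(66.4 × 0.1716) − 1.96) = Φ(1.75) = 96%; simulation gives about 99%. The power problem largely goes, but the HR stays near 3.

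**5. Detectable HR at artery level.** HR = exp(2.80 / √(events × 0.125 × 0.875)) for 80% power: about 5.6 at 24 events and about 11.5 at 12. Using the patient share of 22% would give about 4 and 7, which are wrong for an artery-level analysis.

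**6. Endpoints side by side.** Secondary outcomes: unilateral anterior-circulation events. Sample size: next ischemic event, a term that Secondary outcomes defines to include cardiovascular events. Imaging and statistical analysis: cerebrovascular and cardiovascular events. The window differs too: twelve months in Secondary outcomes, up to 36 months in the Abstract and Background.

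**The case against.** The strongest reply is that the Sample size section states its hazard ratio for ischemic events in general and compares patients, not arteries. If HR 5 is already a patient-level effect, nothing is diluted and 300 patients give about 90% power. The documents do not settle this, so the size of the dilution is conditional. That part stands.

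Follow-up also stands. The Discussion extends clinical follow-up to 36 months, and counts silent lesions on the 12-month MRI, expressly to improve power. A reader might infer that the 300-patient statement fails for the endpoint actually analysed. The documents do not support this: it needs an even split by side, a purely plaque-side HR and a 12-month window all at once. The comfort is conditional too, because the Discussion says recurrence rates have fallen and cannot be estimated precisely.

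Restricting a patient-level analysis to plaque-side events has a price. At s = 0.5 it leaves 15.7 of 24 events and 75% Schoenfeld power, still above 61%. An artery-level analysis keeps events on both sides, with unaffected arteries as comparators.

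It can also be said that the other-territories wording might cover the opposite carotid, or that side is a detail for the full plan. The article does not say the former. As to the latter, it does fix which events count, and that rule admits either side.

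**Conclusion.** The point holds as a badly fixed endpoint. Read literally, opposite-hemisphere events enter the analysis of plaque risk, against the study's own mechanism, and three sections describe different recurrence endpoints. If HR 5 is plaque-side only, the patient-level estimate falls to about 4 at a 25% contralateral share and about 3 at 50%. Longer follow-up improves precision but does not remove that dilution. The effect on power ranges from small to material at 12 months and is minor at 36 months if 8% per year persists. Severity is moderate: the outcome is secondary, and the primary prevalence analysis is unaffected.

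**What to change.** Define the main recurrence endpoint as an ischemic event in the territory of the carotid artery carrying the AHA-LT VI plaque. Analyse it with the artery as unit: exposure is AHA-LT VI in that artery, the event is one in its territory, and Cox regression uses robust variance clustered on patient. Include index side versus other side as a covariate or stratum. Plaques sit almost entirely on the index side, so otherwise a higher recurrence risk on that side would be read as a plaque effect. Keep the any-side unilateral count as a supportive analysis.

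Align Secondary outcomes, Sample size, and Imaging and statistical analysis on this endpoint. State in Sample size the side, event type and follow-up to which the 8% and the hazard ratio of at least 5 apply. Any restated detectable HR must use the artery-level exposed share of about 12.5%, not 22%; the 5.6 and 11.5 above are for an unstratified analysis.

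Cost: wording, somewhat more analysis work, and a less favourable stated detectable HR. No extra patients are needed, and side must already be known to call an event unilateral.

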### Assessment

All patients included into the study are interviewed and examined within 7 days after stroke onset. Assessment at 3, 24 and 36 months follow up is performed using a structured telephone interview conducted centrally by the coordinating center (LMU Munich). Twelve month follow up consists of a clinical examination by a stroke neurologist, blood investigations as well as repeated carotid and brain MRI. Table 2 gives a detailed schedule of planned assessments and time points. In cases where no contact with the patient can be established, information will be obtained from the Residents’ Registration Office.

**Table 2 T2:** Schedule of assessments

**Month**		**0**	**3**	**12**	**24**	**36**
Informed consent		X				
**Interview**						
Demographic variables, migration status		X				
Living situation and level of independence		X	X	X	X	X
Vascular risk factors		X				
Family history (cardiovascular diseases)		X				
Health history (cardiovascular & neurological diseases)		X				
Medication		X	X	X	X	X
Incident cardiovascular & neurological diseases			X	X	X	X
**Neuropsychological Examinations**						
	Montreal Cognitive Assessment (MoCA)	X		X		
	Mini Mental Status Examination (MMSE)	X		X		
	Modified Telephone Interview for Cognitive Status (TICS)		X		X	X
**Clinical Examinations**						
	Anthropometry (Weight, Height, Waist circumference)	X		X		
	Blood pressure	X		X		
	Physical & neurological examination	X		X		
	National Institute of Health Stroke Scale (NIHSS)	X		X		
	Modified Rankin Scale (mRS)	X	X	X	X	X
	Barthel Index (BI)	X	X	X	X	X
**Technical Examinations**						
Blood draws for biobanking, laboratory investigations		X		X		
electrocardiography (ECG)		X		X		
24-hour ECG		X				
Screening ultrasound of the carotid arteries		X				
Transoesophageal and transthoracic echocardiography		X				
Cerebral Magnetic Resonance Imaging (MRI)		X		X		
High resolution black blood carotid MRI (carotid MRI)		X		X		
Contrast enhanced ultrasound (CEUS)		X				

#### Clinical and neuropsychological assessment

Information about demographics, living situation, functional outcome, lifestyle habits, health and family history as well as medication before stroke are provided by the patient or the next of kin. Cardiovascular Risk Factors are defined according to current guidelines [26]. Cognitive function is investigated using the Mini Mental State Examination (MMSE) [27] and the Montreal Cognitive Assessment (MoCA) [28]. The Informant Questionnaire on Cognitive Decline in the Elderly (IQCODE) [29] will be performed in subjects scoring below 27 in the MoCA. Clinical examination consists of anthropometric measures and a standardized neurological examination. Stroke severity is assessed by a certified stroke neurologist using the National Institutes of Health Stroke Survey (NIHSS). The modified Rankin Scale (mRS) and the Barthel Index (BI) serve as measures of functional outcome.

#### *Brain MRI*

Unilateral infarct localization within the anterior circulation is confirmed by brain MRI. Infarcts are defined as acute diffusion restrictions (hyperintensities) on Diffusion weighted images with corresponding hypointense areas on ADC maps. In addition T2-weighted and FLAIR sequences are acquired.

#### *Ultrasound*

Ultrasound investigations include assessment of extra- and intracranial vessels by Doppler and color duplex sonography. Specifically, the following measures are obtained: plaque thickness, plaque localization (< 1 cm proximal or distal to carotid bifurcation), plaque configuration (eccentric or concentric), echogenicity (hypo-, iso- or hyperechoic) and stenosis grade according to NASCET criteria.

#### *Cardiac examinations*

Cardiac examinations include transthoracic (TTE) and transesophageal echocardiography (TEE), 12-lead ECG and Holter monitoring for 24 hours. Routine TEE includes a search for right-to-left shunt (patent foramen ovale), atrial septal aneurysm and intracardiac thrombi. For research purposes the ascending aorta, the aortic arch and the proximal portion of the descending aorta is examined with respect to aortic plaques, defined as irregular thickening of the vessel wall of > 3 mm thickness [30].

#### *Blood tests*

Serum and plasma samples are taken for laboratory investigations including parameters of inflammation (e.g. hs-CRP, interleukin), lipid status and for future analyses of biomarkers that will emerge during the study. Biosamples are processed using standard operating procedures harmonized with the Munich biotech cluster m4 (http://www.m4.de).

#### *Stroke classification*

All initial strokes and recurrent events will be classified according to the TOAST and ASCO classification and both classification schemes will be used for the final analyses. The Classification is carried out by two experienced raters ([name], [name]) who are blinded with regard to the results of carotid MRI. In case of discrepancy, a consensus will be reached by discussion.

#### *Carotid MRI*

All subjects are imaged twice (baseline and 12 month follow up) using a multi-sequence protocol [31] (Time-of-flight MR angiography (TOF-MRA), axial pre- and post- contrast black-blood T1-, PD- and T2- weighted sequences with fat suppression; best in-plane resolution 0.5 × 0.5 mm^2^) at 3 Tesla (Siemens Verio, Siemens Healthcare, Erlangen, Germany) with a dedicated 4-channel surface coil (Machnet B.V., Eelde, the Netherlands). Parallel imaging is used for all sequences with a parallel acquisition technique (PAT) acceleration factor of 2 for T1-, PD- and T2- weighted sequences. The protocol results in a total imaging time of 22:43 minutes for the carotid MRI. Gadolinium-DTPA-BMA (Gadobutrol, Bayer Schering, Leverkusen, Germany) of 0.1 mmol/kg (0.1 ml/kg) is given at a rate of 3 ml/s. Post-contrast T1w imaging is performed approximately 5 minutes after intravenous injection of the contrast agent. Fat suppression is used for pre- and post-contrast T1w, PDw, and T2w images to reduce signals from subcutaneous and perivascular fat. Each scan covers 30 mm (2 mm slice thickness × 15 matched images across the 5 sequences).

#### Dynamic contrast-enhanced carotid MRI

In the subgroup of patients included at the coordinating center (LMU Munich), an additional dynamic contrast-enhanced (2D-Saturation-Recovery Spoiled Gradient Echo) MRI series of the carotid arteries is acquired over five minutes after contrast administration consisting of two representative axial slices with a sampling interval of 1.8 seconds each. Using a PAT factor of 4, best in-plane resolution is 0.625 x 0.625 mm^2^. This sequence is acquired between the pre- and post-contrast T1-weighted sequences. The aim of this sub-study is to visualize markers of plaque vulnerability, such as neovascularization and inflammation [32] and to test whether increased plaque vascularization is associated with an increased progression rate and with a higher rate of stroke recurrence.

#### 18-Fluor-deoxyglucose positron emission tomography - MRI (18 F-FDG PET/MRI)

For a subgroup of patients recruited at the Technical University of Munich a novel, fully integrated PET/MR system (Biograph mMR, Siemens Healthcare, Erlangen, Germany) is used for the baseline scan. In addition to full 3 T-MRI capabilities including the acquisition of the aforementioned morphologic MRI-sequences, this hybrid PET/MR system permits the simultaneous acquisition and co-registration of a PET-dataset. To investigate the potential increase in diagnostic information provided by quantitative measures for the uptake of 18 F-FDG, patients are administered approx. 5 MBq/kg body weight of 18 F-FDG in combination with 20 mg of furosemide via i.v. bolus injection 3 hours prior to the baseline scan. Simultaneous acquisition of MRI-sequences and PET data is performed in analogy to the protocols published for cardiac imaging [33]. This additional PET-scan was approved by the Federal Office for Radiation Protection (Bundesamt für Strahlenschutz, BfS). The aim of this sub-study is to quantify plaque inflammation and to correlate plaque inflammation as assessed by PET/MRI to plaque morphology as assessed by carotid MRI. Furthermore, it will be tested whether increased plaque inflammation is associated with an increased progression rate and with a higher rate of stroke recurrence.

#### Contrast-enhanced ultrasound

Contrast enhanced ultrasound (CEUS) with a microbubble based contrast agent (SonoVue®, Bracco, Italy) will be applied in a subset of patients without risk factors for ultrasound contrast agents. The aim of this sub-study is to visualize markers of plaque vulnerability, such as plaque ulceration or neovascularization in the intima and the plaque [34] and to test whether increased plaque vascularization by ultrasound is associated with an increased progression rate by carotid MRI. Plaque vascularization will be graded on a 4-point scale (0 = absent, 1 = little, 2 = moderate and 3 = strong). Furthermore, the origin of the neovasculature will be recorded (1 = from the vessel wall, 2 = from the lumen). In addition presence or absence of plaque ulceration will be recorded.

### Sample size

Based on a pilot study by Freilinger et al. [24], we estimated that 40% of ipsilateral carotid artery plaques in patients with a cryptogenic stroke are complicated AHA-LT VI plaques. Thus, in 100 patients with cryptogenic stroke the prevalence can be assessed with a precision of +/− 10%. Our unpublished pilot data indicate a prevalence of complicated AHA-LT VI plaques in patients with defined stroke etiology of about 10%. To determine this difference with a power of 80% and 5% level of significance, 32 patients of each group (cryptogenic and control group) would be sufficient. Assuming a prevalence of complicated AHA-LT VI plaques of 30% in the cryptogenic stroke group, 64 patients in each group are needed.

The recurrence rate of ischemic stroke associated with complicated AHA-LT VI plaques will be determined as the time period until the next ischemic event. Assuming a recurrence rate of ischemic events of 8% [35] within 12 months following the index stroke and a hazard ratio of AHA-LT VI plaques ≥ 5 [19,34,35], 300 patients will be enough to demonstrate a significant difference in event rates between patients with and without AHA-LT VI plaques.

Previous longitudinal studies, which demonstrated associations of intraplaque hemorrhage with accelerated plaque progression and with new surface disruption, were able to show those associations with much smaller sample sizes [21,36]. Thus 300 patients will provide sufficient power to detect effects of certain plaque features on plaque progression.

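### The recurrence endpoint is defined by conflicting event sets: the Sample size section counts any next ischemic event, while Secondary outcomes puts unilateral anterior-circulation events into the recurrence analysis

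*Protocol article*

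**What the plan says.** Four places in the protocol article bear on what counts as a recurrence.

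- **Sample size.** "The recurrence rate of ischemic stroke associated with complicated AHA-LT VI plaques will be determined as the time period until the next ischemic event". The same paragraph assumes that 8% of patients have an ischemic event within 12 months, takes a hazard ratio of at least 5 for AHA-LT VI plaques, and concludes that 300 patients suffice.
- **Secondary outcomes, definition.** "Recurrent ischemic events include cerebrovascular and cardiovascular events". The cerebrovascular part covers clinical events, new lesions seen on MRI alone, and the two combined.
- **Secondary outcomes, use.** "Unilateral events in the anterior circulation will be included in the final analysis to estimate the risk of recurrent events". The remaining events have another purpose: "Recurrent ischemic events in other territories, bilateral events and cardiovascular events (myocardial infarction, vascular death) are recorded during follow-up to evaluate" whether plaque-positive patients carry more atherosclerotic disease overall.
- **Imaging and statistical analysis.** Cox regression is planned for "The effect of plaque morphology on cerebrovascular (TIA, amaurosis fugax and stroke) and cardiovascular events (myocardial infarction, vascular death"). The closing lines of that section plan Kaplan-Meier curves and Cox regression for recurrence of cerebrovascular events, compared between stroke subtypes.

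**The concern.** The Sample size sentence names one quantity, recurrence of ischemic stroke linked to the plaque, and derives it from a broader one, time to the next ischemic event. The article itself defines that broader term to include myocardial infarction and vascular death. Secondary outcomes separates these events, and cerebral events in other territories, from the recurrence-risk analysis.

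The main longitudinal question is whether a complicated carotid plaque raises the risk of a new event of the kind it could cause. Events with a weaker link to the plaque would pull the hazard ratio toward 1. In a time-to-first-event analysis, an early non-qualifying event would also hide a later qualifying one. With several event sets in the text, the choice among them could be made after the data are seen.

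**Working it through.** **1. The event sets side by side.** Each row is read literally from the article.

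| Place | Unilateral anterior clinical event | Other-territory or bilateral cerebral event | MRI-only lesion | Myocardial infarction, vascular death |
|---|---|---|---|---|
| Sample size, with the Secondary outcomes definition | counts | counts | counts | counts |
| Secondary outcomes, recurrence risk | counts | kept for disease burden | counts if unilateral anterior | kept for disease burden |
| Imaging and statistical analysis, Cox on plaque morphology | counts | counts (no territory limit) | not listed | counts, jointly or separately (not stated) |
| Imaging and statistical analysis, stroke subtypes | counts | counts (no territory limit) | counts by the general definition | not included |

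No two rows agree.

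**2. Three patient records.**

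- Myocardial infarction at month 4, no stroke: an event at month 4 under Sample size; none under the Secondary outcomes rule.
- Posterior-circulation stroke at month 6, unilateral anterior stroke at month 20: month 6 under Sample size; month 20 under Secondary outcomes.
- Vascular death without stroke: an event under Sample size; none under Secondary outcomes.

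**3. The plan's own figure.** 300 × 0.08 = 24 events at 12 months. The 300 cannot be reproduced exactly, because neither power nor the plaque-positive share is stated for this comparison. With hazard ratio 5, two-sided 5% and 80% power (the last two assumed), Schoenfeld's formula needs 34, 24 and 19 events for plaque-positive shares of 10%, 15% and 20%. At 8% these correspond to 425, 300 and 238 patients. One hundred cryptogenic patients at 40% and 200 others at 10% give (40 + 20)/300 = 20%, at which 24 events yield 88% power. So 300 is consistent with the plan's inputs if all 24 events carry a hazard ratio of 5 and the share is at least about 15%.

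**4. Illustration of dilution.** Inputs:

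- Plaque-positive share p = 0.4 × 0.40 + 0.6 × 0.10 = 0.22. The 40% and 10% prevalences are from Sample size. The 40% cryptogenic share is from the first 79 patients (Table 3), and the 10% is applied to all other patients.
- Hazard ratio 5 for qualifying events (plan) and 1 for the others (assumed).
- Share q of the 8% that is unilateral anterior: not in the documents, so 0.7, 0.6 and 0.5 are tried.

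Plaque-negative rate of qualifying events: a = 0.08q/(0.78 + 5 × 0.22) = 0.08q/1.88. Rate of other events: b = 0.08(1 − q). Blended hazard ratio: (5a + b)/(a + b).

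- q = 0.7: a = 0.0298, b = 0.024; 0.1729/0.0538 = 3.2
- q = 0.6: a = 0.0255, b = 0.032; 0.1597/0.0575 = 2.8
- q = 0.5: a = 0.0213, b = 0.040; 0.1464/0.0613 = 2.4

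**5. Does this make 300 too few?** Qualifying events at 12 months would be 24q = 16.8, 14.4 and 12.0. Schoenfeld's formula asks for 7.849/(0.22 × 0.78 × (ln 5)²) = 17.7. However, a simulation of 4,000 cohorts of 300 (exponential times, log-rank test with cut-off 1.96) gives 12-month power of 89%, 85% and 79% when only qualifying events are counted, and 79%, 68% and 56% under the literal Sample size rule. At 36 months the figures are at least 99% and at least 90%. Schoenfeld's approximation is pessimistic at this hazard ratio and split, so the shortfall against 17.7 does not establish low power.

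**The case against.** The strongest reply is that the sentence sits in a sample-size justification, that Secondary outcomes gives the specific rule for the final analysis, and that the specific rule should prevail. Because the subject of the sentence is ischemic stroke, its final words could also mean the next cerebrovascular event. This has force: Sample size is not the only rule, and a reader might infer that myocardial infarctions will be scored as stroke recurrences, which the text does not make certain. It does not dissolve the conflict, because the article defines the term broadly and the analysis section, where the matter should be settled, uses neither the Secondary outcomes set nor a single set of its own.

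Second, the dilution is assumed. The documents give no split of event types, and a hazard ratio of exactly 1 for other events sits uneasily with a plan that records them to test for higher disease burden. Any value between 1 and 5 shrinks the effect. That stands, so the figures are an illustration.

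Third, a reader might infer that 300 patients are too few. The documents do not support this. The simulation contradicts it under the Secondary outcomes rule, the plan's hazard ratio is at least 5, and the Discussion extends clinical follow-up to 36 months and counts silent lesions to gain power.

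Fourth, whether the 8% includes cardiac events depends on a cited source that is not at hand, so it cannot be said to be too broad.

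Finally, the Secondary outcomes rule does not require the event to be on the side of the plaque, so adopting it would not exclude every unrelated event.

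**Conclusion.** The contradiction is real and lies in the article's own wording. Sample size, Secondary outcomes and the two Cox descriptions do not name the same events, so the recurrence hazard ratio is not uniquely defined. Under the literal Sample size rule it would be a different quantity from the one Secondary outcomes intends, and a smaller one if the additional events are less related to the plaque. The illustrative fall from 5 to between 3.2 and 2.4 rests on an assumed qualifying share of 70% to 50%, an assumed hazard ratio of 1 for other events and a derived plaque prevalence of 22%. Its size in this cohort cannot be obtained from the documents.

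The issue affects a secondary outcome and should be corrected. It does not touch the primary prevalence comparison.

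**What to change.** Use one definition in Sample size and in both parts of Imaging and statistical analysis, matching Secondary outcomes: recurrence is the time from the index event to the first unilateral anterior-circulation cerebrovascular event. In addition:

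- State whether lesions seen only on MRI count in the time-to-event analysis.
- State that non-fatal myocardial infarction and other-territory or bilateral events do not count as recurrence and do not end follow-up for it.
- Analyse these events and vascular death as a separate disease-burden endpoint.
- In Sample size, state which event types the 8% covers. If it is broader than the analysed events, restate the expected number of qualifying events.

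The cost is a few sentences. Secondary outcomes already provides for recording all these event types, so no new data collection is needed. The downside is fewer counted events in the recurrence analysis.
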